
### Ethical approval

The study protocol has been approved by the accredited Dutch Medical Ethical Trial Committee (METC) of the Erasmus University Medical Centre (registered under number NL31406.097.10 and file number P13.258). According to the Dutch Data Protection Act (DPA) data will be safely stored and anonymized and is only accessible for members of the research group or the Medical Ethical Committee. All patients will provide informed consent before entering the study.

### Sample size/power

Following the CONSORT statement we calculated our power to the primary outcome measure of this study and not for the secondary or tertiary outcome measures. Based on previous findings and study protocols [33,60], we expect a difference of 65 to 85 percent (an absolute difference of 20%) of accepted depots between the control group and the money-for-medication condition. In terms of Cohen’s h, this constitutes a medium effect size (h =0.5). With Type I error rate (alpha) set at 5%, power at 0.90 (1 – Type II Error rate; 1-β), and 20—25% drop-out, we will need 84 patients per arm to detect an absolute difference of 20% [61]. In total 168 patients will be included.

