**Methods/Design:**

Outpatients (n =168) with a psychotic disorder will be randomly assigned to either the experimental group (n =84), receiving a financial reward for each accepted antipsychotic medication depot, or the control group (n =84), receiving treatment as usual without financial rewards. Patients are included regardless of their previous adherence. The intervention has a duration of twelve months. During the subsequent six months follow-up, the effects of discontinuing the intervention on depot acceptance will be assessed.

The primary goal of this study is to assess the effectiveness of providing financial incentives for improving adherence with antipsychotic depot medication (during and after the intervention). The primary outcome measure is the percentage of accepted depots in comparison to prescription. Secondary, we will consider alternative measures of medication acceptance, i.e. the longest period of uninterrupted depot acceptance and the time expired before depot is taken. Additionally, the effectiveness of the experimental intervention will be assessed in terms of psychosocial functioning, substance use, medication side-effects, quality of life, motivation, cost-utility and patients’ and clinicians’ attitudes towards M4M.

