#### Hypotheses

The primary hypothesis is that M4M results in significantly more accepted depots than treatment as usual (TAU). Patients from both the TAU and M4M condition are prescribed antipsychotic depot medication. Secondary hypotheses are that M4M, compared to TAU, leads to (1) longer uninterrupted periods of depot acceptance and (2) less time expired before the depot is taken. From our tertiary measures, we expect M4M (compared to TAU) to result in (3) less severe symptoms and better psychosocial functioning, (4) improved quality of life, (5) less substance use, and (6) lower costs.

Using exploratory analyses we will look for patient characteristics (at baseline) – the stratification variables (gender, comorbid substance use, and medication adherence) and, other variables including impulsivity, motivation and attitudes towards antipsychotic medication and M4M – that could moderate the effects of M4M and might be used for future patient treatment matching. In addition, we will explore the role of potential mediating variables – e.g., medication side effects – in M4M’s effectiveness. Finally, we will analyze self-reported data on patients’ and clinicians’ perceptions of M4M. This enables us to discuss the ethical considerations of M4M.

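### 84 per arm is the two-sided answer before any drop-out and at h rounded up from 0.47 to 0.50; with the stated 20–25% loss the power is about 75–78%, not 90%

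*Protocol article*

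**What the plan says.** All the inputs stand in one paragraph of the protocol article, Sample size/power, which says that the calculation was made for the primary outcome.

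- Rates: "we expect a difference of 65 to 85 percent (an absolute difference of 20%) of accepted depots", control against incentive arm.
- Effect size: "this constitutes a medium effect size (h =0.5" on Cohen's scale.
- Error rates: "With Type I error rate (alpha) set at 5" per cent, with power 0.90.
- Drop-out: 20–25%, listed in the same sentence as alpha and power.
- Result: "we will need 84 patients per arm to detect an absolute difference of 20" per cent, and "In total 168 patients will be included".

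The Abstract repeats the arm size: patients "will be randomly assigned to either the experimental group (n =84" or to a control group of the same size. The article gives neither the number of evaluable patients before inflation nor whether the test is one- or two-sided.

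**The concern.** As written, 84 per arm is the number to randomise so that 90% power remains after 20–25% of patients are lost. Yet 84 is almost exactly what the usual two-sided formula returns for h = 0.50 and 90% power with nobody lost. If so, the drop-out allowance was named but never added. Separately, the h in the text is larger than the h that follows from the two percentages beside it, and a larger h makes the required sample smaller. Both errors act in the same direction.

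What is at stake is how the result is read. A null finding would be presented as coming from a design with a 10% chance of missing a 20-point difference, when the stated inputs imply a chance more than twice as large.

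**Working it through.** **Inputs**, all from Sample size/power: 65% and 85%; stated h = 0.5; alpha 5%; power 0.90; drop-out 20–25%; 84 per arm, 1:1. Sidedness is not stated; two-sided is taken as the conventional reading and one-sided is checked below.

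**Step 1: reproduce the plan's figure.** For Cohen's h, the number per arm is n = 2(z_alpha + z_power)² / h². Two-sided 5% and 90% power give z-values 1.95996 and 1.28155, so

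n = 2 × (3.24151)² / 0.50² = 21.015 / 0.25 = **84.06**.

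This matches the stated 84 with no allowance for loss. Applying the stated loss by dividing by (1 − d) gives 84.06 / 0.80 = 105.1 and 84.06 / 0.75 = 112.1 per arm.

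**Step 2: recompute h from the stated rates.**

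h = 2·asin(√0.85) − 2·asin(√0.65) = 2.3462 − 1.8755 = **0.4707**.

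Then n = 21.015 / 0.4707² = **94.85**, that is 95 evaluable per arm, or 94.85 / 0.80 = 118.6 (119) to 94.85 / 0.75 = 126.5 (127) randomised per arm.

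**Step 3: power that 84 per arm provides.** Losing 20–25% leaves 84 × 0.80 = 67 to 84 × 0.75 = 63 per arm. Two-sided power is Φ(h·√(n/2) − 1.96); for example, at h = 0.4707 and n = 67, Φ(0.4707 × 5.788 − 1.96) = Φ(0.764) = 0.778.

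| Analysed per arm | Two-sided, h = 0.50 | Two-sided, h = 0.471 | One-sided, h = 0.50 | One-sided, h = 0.471 |
|---|---|---|---|---|
| 84 (no loss) | 90.0% | 86.2% | 94.5% | 92.0% |
| 67 (20% loss) | 82.5% | 77.8% | 89.4% | 86.0% |
| 63 (25% loss) | 80.1% | 75.2% | 87.7% | 84.1% |

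As a cross-check, the pooled two-proportion formula for 65% against 85%, two-sided, needs 97 evaluable per arm and gives 76.8% to 74.2% with 67 to 63 analysed.

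**Step 4: other routes to 84.**

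- One-sided 5%, 90% power, h = 0.50 needs 68.5 per arm. Multiplying by 1.20 to 1.25 gives 82.2 to 85.6, which includes 84. The correct inflation, dividing by (1 − d), gives 85.6 to 91.3; on that footing 84 covers a loss of 1 − 68.5/84 = 18%.
- Two-sided, 80% power, h = 0.50 with 25% loss gives 83.7, but that contradicts the stated power of 0.90.

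At the stated rates a one-sided test would need 77.3 / 0.80 = 96.6 (97) to 77.3 / 0.75 = 103.1 (104) per arm.

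**The case against.** Four points can be made for the plan.

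*Sidedness.* The article does not state it, and the hypothesis is directional: "The primary hypothesis is that M4M results in significantly more accepted depots than treatment as usual (TAU". A one-sided test with multiplicative inflation can reach 84 with drop-out included. This stands to the extent that the missing allowance is an inference from the exact two-sided match. It does not rescue the figure: a directional hypothesis does not declare a one-sided test, and after the stated loss that reading still gives 89.4% to 87.7% at h = 0.50 and 86.0% to 84.1% at h = 0.471.

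*Loss of primary data.* Table 1 has depot acceptance recorded continuously on registration forms, apart from the interviews, so patients who stop interviews may still contribute to the primary outcome. This is fair, and actual loss may be smaller than 20–25%. But the article names drop-out as an input to the primary-outcome calculation, and with no loss at all power is 86.2%.

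*The outcome is not binary.* The medication possession ratio is a proportion per patient, to be analysed with generalized linear models. Its variance cannot exceed the binary value, which corresponds to an average SD of 0.42. For a simple two-sided comparison of means with 63–67 per arm, assumed SDs of 0.40, 0.35 and 0.30 would give power of 80–82%, 89–91% and 96–97%. So 75–78% is not a statement of the trial's true power. However, the article gives no SD and makes no such argument; it uses Cohen's h on two percentages, and its claim has to be judged by that method.

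*Rounding.* Writing 0.471 as 0.5 may be seen as one-decimal rounding. On its own it costs about 4 points of power (90.0% to 86.2%), the smaller of the two errors.

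**Conclusion.** The concern holds: the sample-size statement is wrong as written. On the stated 65% against 85% and 20–25% drop-out, 84 per arm does not give 90% power whether the test is one- or two-sided. On the conventional two-sided reading it gives 77.8% to 75.2%, a type II error of about 22–25% against the stated 10%. Keeping the rounded h, it gives 82.5% to 80.1%.

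These figures assume a two-sided 5% test, one binary result per patient as the plan's own method implies, and no primary-outcome data from patients who drop out. Relaxing the first or the third assumption alone raises power to 84–86% and 86% respectively. Only if both are relaxed, with a one-sided test and no loss at all, does power pass 90% (92.0%), and that sets aside the drop-out the plan itself specifies. That h is 0.471 rather than 0.5 depends on none of these assumptions.

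**What to change.** Reword the Sample size/power paragraph and leave the sample size as it is. For example:

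> An acceptance of 65% against 85% corresponds to Cohen's h = 0.47. With a two-sided 5% test, 84 patients per arm give 86% power if primary-outcome data are complete, 78% with 20% loss and 75% with 25% loss.

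If a one-sided test was intended, the paragraph must say so and carry the one-sided figures instead (92%, 86% and 84%). It should also say whether the 20–25% refers to the interviews or to the depot registration. Table 1 already provides for continuous recording of acceptance; stating that these records will be used for every randomised patient, including those who stop interviews, would bring the design closer to the 86% figure.

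The cost is one paragraph and a less favourable stated power; no extra patients are needed. Holding 90% at the stated rates and drop-out would instead take 119 to 127 per arm, 238 to 254 in total.

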### Statistical analyses

The primary outcome will be reported as accepted depots as percentage of planned depots, most often weekly, biweekly or monthly. The effects of the intervention on our outcome measures will be analysed using generalized linear models as appropriate to the outcome, with random effects for sites or treatment teams. Sensitivity analyses will be conducted to explore the impact of different strategies for handling missing data. A detailed analysis plan will be completed prior to analysis of baseline measurements.

## Discussion

The aim of the current randomized controlled study is to assess the effectiveness of financial incentives (M4M), compared to treatment as usual, in improving the acceptance of antipsychotic depot medication in patients with psychotic disorders. Our primary outcome measure will be the MPR. Secondary outcome measures include patients’ health, social and psychological functioning and subjective quality of life. Tertiary measures are used to assess the effects of medication acceptance on patients’ psychosocial functioning, substance use, quality of life and side effects of the antipsychotic medication. This allows us to assess not only whether M4M is an effective intervention to improve acceptance, but also to what extent medication acceptance contributes to patients’ wellbeing We will also compare the MPR during the follow-up period (six months), in which no CM takes place.

### The use of financial incentives in M4M

In the pilot study of Claassen et al. [34], M4M did not have a negative impact on the therapeutic relationship. Furthermore, they have not found that other patients who did not participate in the M4M study complained about unequal treatment or demanded to be paid for taking medication as well.

In the pilot study of Staring, Mulder, and Priebe [35], all five participants considered M4M to be a good project. The reasons they gave to participate in the pilot were “I don’t like the injection, but money makes it better”, “Money keeps me motivated”, and “The depot injections keep me balanced”. When prompted, two patients said that they perceived financial incentives as a voluntary and non-coercive measure, two patients did not know what to think about this, and one indicated that he perceived financial incentives as a coercive measure, saying that “I have to take the medication anyway”. All patients said that they spent the money on food and cigarettes, and one patient also bought household products. It was observed, however, that at least one patient had spent some of the money on cannabis. Other patients did not ask to be offered incentives as well and no negative impacts on therapeutic relationships were noted. Some patients however felt that they should receive more money (they received 10 euro for every two weekly depot, 15 euro for every three-weekly depot and 20 euro for every four-weekly depot).

Although higher payments have been found to result in bigger effects [62,63], in the present study we have chosen a maximum of 30 euro’s on average per month because (1) patients could get used to or become financially dependent on higher payments or even lose their social security benefits and (2) to strive for acceptable cost-utility of M4M. From a societal perspective it is important to focus on cost-effective interventions and given the results of prior research [35], it seems not necessary to use higher incentives.

### Strengths and limitations

Our study started in 2010, prior to some of the recent findings as described above. The difference with the earlier RCT studying the effects of M4M [36] is that we will include both patients who are partially non-compliant, as well as patients who are compliant in taking depot medication. The rationale to also include compliant patients is the observation in several studies that around thirty percent of patients initiated on antipsychotic depot medication cease to accept their depot within one year [5,64,65]. In addition, when we eventually might want to implement this intervention into daily clinical practice, it is more ethical as well as more practical to reward both compliant and non-compliant patients.

A possible limitation of this study are the different medication depots. Although most patients receive medication injections it is also allowed for patients to take oral penfluridol. The disadvantage of this oral antipsychotic medication is that it is more difficult to check if patients actually take their medication. However, penfluridol is also a depot and because we aim to test if our intervention is broadly applicable we decided to include both patients with oral penfluridol and injections.

Another limitation is that the clinicians cannot be blinded to the intervention condition, possibly resulting in a more stimulating attitude for accepting depot medication in the intervention group. Also, the interviewers are not blind to the patients’ condition and therefore can rate patients’ responses as more positive or negative.

Furthermore, the intervention effect can be influenced by different depot frequencies. For example, patients who receive money every week are rewarded four times as often compared to patients that receive depot every month. Receiving a small incentive more frequently can be more stimulating or motivating compared to receiving a bigger incentive only once a month. This can interfere with our intervention effect, even though the mean amount of money per month remains equal for all participants.

### Ethical issues

Ethical concerns have been raised about paying patients to accept their medication and whether this is an acceptable means in the treatment of patients with psychotic disorders [66,67]. One of these concerns is that patients’ intrinsic motivation to accept medication will disappear if money is involved. We will study this by assessing intrinsic motivation over time, as possible decreases in depot acceptance can occur during the 6 month follow-up without M4M. Another frequently raised ethical argument is that patients might buy drugs or alcohol from the money they receive. We will monitor alcohol and drug use by using assessment scales as well as obtaining urine samples.

Apart from these ethical concerns, we will also assess the intervention from a cost-utility perspective, because this is an important factor to consider from a societal point of view. In conclusion, we will test if M4M improves patients’ MPR, reduces their psychotic symptoms and contributes to a clinical improvement.
